### Matching Strategy

Recovered controls will be individually matched 1:1 to Long COVID cases without replacement to improve baseline comparability. Matching will require exact matching on sex/gender, with flexibility of ±3 years for age and ±30 days for date of acute COVID-19 diagnosis. When multiple eligible controls are available for a given case, the selected control will be the one minimizing the absolute age difference; if ties remain, the absolute diagnosis date difference will be minimized, with random selection used only if ties persist. Each matched set will be assigned a unique pair identifier (pair_id) and retained in the analytical dataset; participants who cannot be matched within the prespecified calipers will be retained in the study database and considered in prespecified sensitivity analyses.

### Data Collection and Management

After written informed consent is obtained, each participant will be assigned a unique internal study code to ensure confidentiality. The code key linking personal identifiers to the study code will be accessible only to the principal investigator and will be stored separately from study data, in accordance with the General Data Protection Regulation (GDPR) and applicable Spanish data protection legislation. All study information will be recorded and managed using secure electronic data capture procedures; self-administered questionnaires will be completed via REDCap (Research Electronic Data Capture; Vanderbilt University) software [31]. Study datasets will be deidentified/anonymized for analysis and will be stored securely, with participants linked only through the assigned study code.

### Appointments and Procedures

Data collection will be organized into 2 study appointments. During the first appointment, fasting blood samples will be collected for routine laboratory analyses, and participants will sign informed consent covering both study participation and biobank sample storage. Participants will also receive standardized instructions for completing the self-administered questionnaires online through REDCap [31]. The second appointment will include completion of exploratory tests and the collection of any additional clinical or sociodemographic data not captured at the first visit. Standardized procedures will be used at each visit to minimize measurement variability and ensure comparability across participants and across time points. The participant flow and assessment schedule are summarized in Figure 1.

**Figure 1 figure1:**
[figure not shown]
Participant flow diagram. 1MSTST: 1-minute sit-to-stand test; 6MWT: 6-minute walk test; ACC: accuracy; AUC: area under the receiver operating characteristic curve; FSS: Fatigue Severity Scale; HADS: Hospital Anxiety and Depression Scale; IPAQ-SF: International Physical Activity Questionnaire-Short Form; ML: machine learning; PCFSS: Post–COVID-19 Functional Status Scale; PCS: Pain Catastrophizing Scale; PHC: primary health care; PHQ-9: Patient Health Questionnaire-9; PREDIMED: Prevención con DIeta Mediterránea; PSQI: Pittsburgh Sleep Quality Index; RF: random forest; SF-12: 12-Item Short Form Health Survey.

### Variables and Measurements

#### Overview

Study variables will include outcomes related to persistent symptoms and functioning, additional patient-reported outcomes, cognitive performance measures, and laboratory biomarkers, alongside core sociodemographic and clinical covariates. Measurements will be obtained at T0 (baseline) and repeated at T1 (follow-up) using the same instruments and procedures to support longitudinal comparisons. Textbox 1 summarizes the study variables collected for sociodemographic, clinical, lifestyle, psychological/functional, and biological domains.

Study variables.
**Sociodemographic**
Age, sex/gender, place of residence, occupation, education level, and ethnicity
**Clinical (acute COVID-19 episode)**
Date of symptom onset, symptom profile, hospitalization, intensive care unit admission, and diagnostic method (polymerase chain reaction, antigen, and serology)
**Comorbidities**
Cardiovascular disease, diabetes mellitus, chronic respiratory disease, and other chronic conditions
**Lifestyle**
Physical activity level (International Physical Activity Questionnaire), dietary habits (Prevención con Dieta Mediterránea), sleep quality (Pittsburgh Sleep Quality Index), smoking status, and alcohol consumption
**Psychological and functional**
Quality of life (12-item Short Form Health Survey), depression (Patient Health Questionnaire-9), anxiety (Generalized Anxiety Disorder-7), functional status (Post–COVID-19 Functional Status Scale), cognitive flexibility and attention (Stroop Test), processing speed (Symbol Digit Modalities Test), visuospatial memory (Rey-Osterrieth), pain catastrophizing (Pain Catastrophizing Scale), and fatigue severity (Fatigue Severity Scale)
**Biological**
Complete blood count, basic biochemistry, coagulation profile, inflammatory markers (C-reactive protein and interleukin-6), cytokine profile, and SARS-CoV-2 serology

#### Primary Outcome

The primary outcome will be Long COVID status (case vs recovered control). Cases will be defined as individuals with confirmed SARS-CoV-2 infection who report persistent symptoms for ≥12 weeks after infection onset, consistent with the WHO definition. Controls will be defined as individuals with a confirmed SARS-CoV-2 infection who report complete recovery, operationalized as the absence of persistent or new symptoms after COVID-19.

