## Introduction

### Overview

The COVID-19 pandemic has substantially reshaped the global health burden by producing not only acute morbidity and mortality but also a spectrum of persistent postinfectious sequelae that continue to affect large numbers of survivors [1-3]. One of the most clinically and socioeconomically consequential of these sequelae is Long COVID, frequently termed postacute sequelae of SARS-CoV-2 infection (PASC), a heterogeneous syndrome comprising persistent, relapsing, or newly emergent symptoms after the acute phase of infection [4-6]. Population and cohort analyses show appreciable heterogeneity in estimates of prevalence across definitions, follow-up intervals, and dominant variants, with many studies reporting persistent symptoms in the approximate 10%-30% range among infected persons depending on case definition and follow-up timing [7-9]. Typical symptom clusters include debilitating fatigue, dyspnea/exertional intolerance, and cognitive dysfunction (often described as “brain fog”), and these complaints occur in individuals across the spectrum of acute disease severity, including those who had mild acute illness [2,8,9].

Mechanistic concepts for PASC are multifactorial and emphasize an interplay of viral, immune, and host-environment factors, including potential viral persistence or residual antigen, dysregulated or protracted immune activation, chronic systemic and tissue-specific inflammation, perturbations of metabolic pathways, and, in some patients, autoimmune sequelae [5,10,11]. Proteomic and metabolomic studies and longitudinal immune profiling have reported persistent alterations in circulating proteins and immune mediators—including reported associations with proinflammatory cytokines such as interleukin-6 (IL-6) and tumor necrosis factor-α—although results vary across cohorts and time points [10,12,13]. At the same time, psychosocial determinants (eg, preexisting psychiatric morbidity, chronic stress, and social isolation) and baseline comorbidity burden (eg, obesity, cardiopulmonary disease, and chronic kidney disease) have been associated with greater acute severity and may influence recovery trajectories, symptom perception, and care seeking after SARS-CoV-2 infection [14-17].

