### Eligibility Criteria

Participants will be included if they have confirmed SARS-CoV-2 infection by polymerase chain reaction, antigen testing, or serology, and are aged ≥18 years. For the Long COVID group, eligibility will require persistence of symptoms for ≥12 weeks after infection onset, consistent with the World Health Organization (WHO) definition. For the control group, complete recovery will be defined as the absence of persistent or new symptoms after COVID-19. Individuals will be excluded if they refuse to participate, report preexisting symptoms similar to Long COVID prior to SARS-CoV-2 infection, or present severe psychiatric disorders or cognitive impairment that preclude informed participation.

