### Statistical Analysis

#### Overview

All analyses will be performed using IBM SPSS Statistics (version 27) and R software (R Foundation for Statistical Computing). Statistical inference will emphasize effect sizes with 95% CIs and clinically interpretable magnitudes; 2-sided tests will be used. Given the observational design, analyses will be interpreted as associations rather than causal effects. For interpretability, candidate “differential factors” will be grouped by temporality: (1) antecedent factors (eg, sociodemographic and preinfection comorbidities), (2) periacute factors (eg, markers of acute COVID-19 severity such as hospitalization/ICU admission and related clinical features), and (3) concurrent correlates measured at baseline in the postacute phase (eg, patient-reported outcome measures and biomarkers at T0). Antecedent and periacute factors will be interpreted as candidate determinants, whereas concurrent measures will be interpreted primarily as phenotypic correlates differentiating Long COVID from recovered controls.

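### Controls may never have had acute symptoms while cases largely must have, so odds ratios for acute symptoms, and less so for hospitalization/ICU, partly reflect the entry rules

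*Protocol article*

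**What the plan says.** **Entry rules.** Under Eligibility Criteria, both groups need "confirmed SARS-CoV-2 infection by polymerase chain reaction, antigen testing, or serology". Cases also need "persistence of symptoms for ≥12 weeks after infection onset", described as consistent with the WHO definition. Under Primary Outcome, controls are "individuals with a confirmed SARS-CoV-2 infection who report complete recovery, operationalized as the absence of persistent or new symptoms after COVID-19". Neither section asks whether a control was ill during the acute infection.

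**Matching and adjustment.** Matching Strategy requires "exact matching on sex/gender, with flexibility of ±3 years for age and ±30 days for date of acute COVID-19 diagnosis". The core adjustment set under Objective 1 names, as examples, hospitalization/ICU admission, vaccination status or epoch, and comorbidity burden. Whether the acute infection was symptomatic is not among them. The sensitivity analyses listed do not include it either.

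**Data and interpretation.** Textbox 1 lists, for the acute episode, "Date of symptom onset, symptom profile, hospitalization, intensive care unit admission". The Statistical Analysis Overview classes acute severity markers and related clinical features as periacute, and states: "Antecedent and periacute factors will be interpreted as candidate determinants". The same paragraph says that results are associations and not causal effects. The primary objective covers antecedent and periacute factors.

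**The concern.** The two groups enter through different doors. A person with a silent infection found by serology meets the control rule. The same person can hardly meet a rule that requires symptoms persisting from infection onset. Such controls have no acute symptoms and, in effect, no hospitalization for acute COVID-19. Every acute feature is therefore rarer in the control group as a whole than among the controls who were ill.

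An acute symptom with no bearing on who develops Long COVID among ill people can then show an odds ratio above 1. Because periacute factors belong to the primary objective and are labelled candidate determinants, a reader could take such a result as information on which acute features matter once someone is ill. Adjusting for hospitalization/ICU does not help when hospitalization/ICU is itself the factor studied, and it does not separate silent from mildly symptomatic infection.

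**Working it through.** **The plan's own figure.** The Sample Size section takes 20% prevalence in controls and an odds ratio of 2.3, hence about 36.5% in cases, with two-sided 5% and 90% power. The Fleiss normal approximation without continuity correction gives 155 per group (power 89.96% at 154 and 90.1% at 155), so the stated 154–155 reproduces. It serves here only as a yardstick: 2.3 is what the plan calls clinically meaningful.

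**Inputs.**
- p: prevalence of an acute feature among people with a symptomatic acute infection, set equal in cases and controls, so the true odds ratio among them is 1. Assumed.
- q: share of controls never acutely symptomatic, in whom the feature is absent. Assumed; the documents give no figure.
- Cases: all symptomatic at first, relaxed below.
- Enrolled so far: 100 per group (Recruitment and Follow-up Progress).

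**Formula.** Prevalence is p in cases and p(1−q) in controls, so

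OR = [p/(1−p)] ÷ [p(1−q)/(1−p(1−q))].

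Example: p=50%, q=20% gives 50% against 40%, OR = 1 ÷ (0.40/0.60) = 1.50. The last column is the chance of p<0.05 with 100 per group, from the two-proportion normal approximation (unmatched, both tails).

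| Feature | q | Cases vs controls | OR | Chance of p<0.05 |
|---|---|---|---|---|
| Symptom, p=50% | 10% | 50% vs 45% | 1.22 | 11% |
| | 20% | 50% vs 40% | 1.50 | 29% |
| | 30% | 50% vs 35% | 1.86 | 57% |
| Symptom, p=80% | 10% | 80% vs 72% | 1.56 | 26% |
| | 20% | 80% vs 64% | 2.25 | 72% |
| | 30% | 80% vs 56% | 3.14 | 96% |
| Hospitalization, p=10% | 10% | 10% vs 9% | 1.12 | 6% |
| | 20% | 10% vs 8% | 1.28 | 8% |
| | 30% | 10% vs 7% | 1.48 | 12% |

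At q=0 every odds ratio is 1.00.

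**If some cases were also never symptomatic.** Let c be that share, so the prevalence in cases is p(1−c). With c=5% and q=30%, the odds ratio falls from 1.86 to 1.68 (p=50%), from 3.14 to 2.49 (p=80%) and from 1.48 to 1.39 (p=10%). With c=q it returns to 1.00.

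**Any acute symptom, yes or no.** This contrast is the most exposed. If no case was asymptomatic, the odds ratio is infinite for any q above zero. With c=2% it is 5.4, 12.3 and 21.0 at q=10%, 20% and 30%.

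**After restriction.** When both members of each pair were symptomatic, the control prevalence is p again and the inflation is 1.00 by definition.

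**The case against.** The strongest reply is that the target population is everyone with confirmed infection. Silent infections belong to it, absence of symptoms is the low end of acute severity, and the all-pairs odds ratio is a legitimate association there. This stands. The estimate is inflated only when read as a contrast among people who had acute illness, so it should not be called spurious without that qualification.

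Several stronger readings are tempting, and the documents do not support them:
- *A never-symptomatic person can practically never be a case.* The Introduction describes Long COVID as including "persistent, relapsing, or newly emergent symptoms after the acute phase of infection", and the case rule leans on the WHO definition. The text does not settle whether new symptoms after a silent infection make a case.
- *The inflation is fixed by construction.* It depends on q. References to a COVID-19 diagnosis, to recovered controls and to a symptom-onset date suggest that q may be small.
- *Severity odds ratios are badly distorted.* Hospitalization is the periacute marker the plan names, and it moves little. The large figures need common symptoms, which become determinants only through the phrase about related clinical features.
- *The plan will claim determinants.* It says candidate determinants, disclaims causality and calls the aim hypothesis-generating.
- *The adjustment terms carry the effect into the other odds ratios.* No calculation here shows this.

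The plan also leaves partial routes open. The adjustment set is given by example, interactions with acute severity are foreseen where justified, and the original protocol in Multimedia Appendix 2 is not shown. None of these states a contrast among symptomatic participants, so they soften the point without answering it.

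**Conclusion.** The concern holds in a limited form. The control rule admits people who never had acute symptoms; the case rule largely, but not certainly, excludes them; and nothing stated in matching, adjustment or sensitivity analysis addresses the difference. Odds ratios for acute features are therefore partly definitional to the extent that controls were never symptomatic. For common acute symptoms the effect can approach or pass the plan's own 2.3 at shares of 20–30%. For hospitalization it is modest, and at a share of 10% it is hardly visible.

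These sizes rest on assumed values of p and q, on equal prevalence among symptomatic cases and controls, and on an unmatched approximation for the rejection rates. The share in each group, which the study can tabulate from data it already collects, decides whether the problem is material.

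**What to change.** 1. Report the share never acutely symptomatic among cases and among controls.
2. For the periacute factors (acute symptom profile, hospitalization/ICU), prespecify a conditional logistic analysis restricted to existing pairs in which both members had a symptomatic acute infection, and show it next to the all-pairs estimate.
3. Describe the all-pairs estimate as the contrast among all infected people. Call a periacute factor a candidate determinant among people with acute illness only if it holds in the restricted analysis.

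Symptomatic status should not become an exact matching factor, and pairs should not be re-matched. Matching on it would remove from those pairs a feature that the primary objective wants to study and would mix two matching regimes. Re-matching would break the retained pair structure.

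The cost is a few sentences in the analysis section, using data already collected. Primary analyses follow T1, so this can still be prespecified. Pairs are lost for these odds ratios only. At a 20% share, with all cases symptomatic, 100 pairs become 80 and intervals widen by about 12% (√(100/80) = 1.118). If the share is near zero, almost nothing is lost.

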#### Secondary Outcomes

Secondary outcomes will encompass patient-reported and performance-based domains including health-related quality of life, physical activity, dietary pattern/adherence, sleep quality, depressive and anxiety symptoms, post–COVID-19 functional status, cognitive performance, as well as pain catastrophizing, fatigue severity, and laboratory biomarkers (biochemistry/hematology/coagulation, inflammatory markers including C-reactive protein [CRP] and IL-6, cytokine profiling, SARS-CoV-2 serology, and viral reactivation serologies such as Epstein-Barr virus [EBV], cytomegalovirus, and herpes simplex virus type 1 [HSV-1]). The presence and severity of persistent symptoms consistent with Long COVID (eg, fatigue, dyspnea, and cognitive complaints), will be operationalized using standardized symptom assessment procedures within the Long COVID group and contrasted with the absence of persistent symptoms in the control group. Symptom severity will be quantified using the prespecified instruments and scales described in the “Sociodemographic and Clinical Variables” section, enabling both between-group comparisons at each time point and within-participant change from T0 to T1.

These outcomes will be analyzed as complementary indicators of disease burden and functioning and as potential correlates of persistent symptom status and its evolution over time.

#### Sociodemographic and Clinical Variables

Key sociodemographic variables will include age, sex/gender, place of residence, occupation, education, and ethnicity. Clinical history related to the acute SARS-CoV-2 infection will include onset date, acute symptoms, hospitalization, and intensive care unit (ICU) admission (if applicable), and the method used for diagnostic confirmation. Preexisting and incident comorbidities will be recorded, including (but not limited to) cardiovascular disease, diabetes, chronic respiratory disorders, and other relevant conditions, to support confounding control and stratified analyses.

#### Lifestyle and Psychosocial Variables

##### Overview

All participant-reported outcomes will be collected at the baseline visit (T0) and repeated at the follow-up visit (T1; ~3 years after T0) using the same administration procedures. Self-administered questionnaires were completed in a standardized order, with staff available to resolve comprehension issues without coaching responses. Neurocognitive tests were administered by trained personnel following published manuals and standardized instructions. A detailed summary of instruments, scoring, recall periods, and key measurement properties is provided in Multimedia Appendix 1 [32-47].

##### Health-Related Quality of Life

Health-related quality of life was assessed using the Spanish 12-item Short Form Health Survey (SF-12; a 12-item short-form measure derived from the 36-item Short Form Health Survey [SF-36]) that captures 8 health domains and yields 2 standardized summary scores: the physical component summary and mental component summary. Scores are computed using Spanish population weights and interpreted against population norms, with higher scores indicating better health status. In the Spanish validation work, the SF-12 showed acceptable metric performance and construct validity; notably, SF-12 items explained approximately 91% of the variance of SF-36 summary components, supporting the adequacy of the short form for estimating physical component summary and mental component summary in Spanish samples. Internal consistency for SF-12 summary measures has been reported in an acceptable-to-good range in Spain (with component reliability typically around α≈.78-.85) [32].

##### Physical Activity

Physical activity over the preceding week was measured using the International Physical Activity Questionnaire (IPAQ). The IPAQ quantifies time spent in activities of different intensities during the last 7 days, allowing the calculation of energy expenditure (eg, metabolic equivalent of task minutes per week) and categorical classifications of activity level. In the Spanish population, the IPAQ demonstrated good reproducibility and expected validity patterns: test-retest reliability was strong (Spearman ρ≈0.81; intraclass correlation coefficient [ICC]≈0.74), while criterion validity versus objective accelerometry was modest (approximately ρ≈0.27) and improved when compared with activity diaries (approximately ρ≈0.38), consistent with typical performance of self-reported physical activity measures [33].

##### Adherence to the Mediterranean Diet

Mediterranean diet adherence was assessed with the 14-item Mediterranean Diet Adherence Screener (MEDAS) developed within the Prevención con Dieta Mediterránea (PREDIMED) framework. The MEDAS is a brief checklist covering key Mediterranean diet targets; responses are summed to a total score from 0 to 14, with higher scores indicating greater adherence. As a dietary pattern screener (rather than a unidimensional psychometric scale), “validity” is primarily supported through its relationship with external criteria: in PREDIMED, the 14-item tool was used alongside a full-length food frequency questionnaire and showed a strong, graded association with obesity-related indices, supporting its capacity to capture meaningful differences in diet quality in high-risk adults [34].

##### Sleep Quality

Sleep quality was measured using the Pittsburgh Sleep Quality Index (PSQI), a 19-item questionnaire assessing sleep during the previous month and yielding 7 component scores (subjective sleep quality, latency, duration, efficiency, disturbances, sleep medication use, and daytime dysfunction) and a global score ranging from 0 to 21; higher scores indicate worse sleep quality. The original PSQI demonstrated strong clinical use and has been widely used in research settings [35]. In the Spanish version, clinometric evaluation supports its use, with internal consistency around α≈0.81 and evidence of diagnostic performance using standard thresholds (with sensitivity in the high 80% range and specificity around the mid-70% range, depending on the criterion) [36].

